## Abstract

**Background:**

This study is a confirmatory efficacy trial of two treatments for winter seasonal affective disorder (SAD): SAD-tailored group cognitive-behavioral therapy (CBT-SAD) and light therapy (LT). In our previous efficacy trial, post-treatment outcomes for CBT-SAD and LT were very similar, but CBT-SAD was associated with fewer depression recurrences two winters later than LT (27.3% in CBT-SAD vs. 45.6% in LT). CBT-SAD engaged and altered a specific mechanism of action, seasonal beliefs, which mediated CBT-SAD’s acute antidepressant effects and CBT-SAD’s enduring benefit over LT. Seasonal beliefs are theoretically distinct from LT’s assumed target and mechanism: correction of circadian phase. This study applies the experimental therapeutics approach to determine how each treatment works when it is effective and to identify the best candidates for each. Biomarkers of LT’s target and effect include circadian phase angle difference and the post-illumination pupil response. Biomarkers of CBT-SAD’s target and effect include decreased pupillary and sustained frontal gamma-band EEG responses to seasonal words, which are hypothesized as biomarkers of seasonal beliefs, reflecting less engagement with seasonal stimuli following CBT-SAD. In addition to determining change mechanisms, this study tests the efficacy of a “switch” decision rule upon recurrence to inform clinical decision-making in practice.

**Methods:**

Adults with SAD (target *N* = 160) will be randomzied to 6-weeks of CBT-SAD or LT in winter 1; followed in winter 2; and, if a depression recurrence occurs, offered cross-over into the alternate treatment (i.e., switch from LT➔CBT-SAD or CBT-SAD➔LT). All subjects will be followed in winter 3. Biomarker assessments occur at pre-, mid-, and post-treatment in winter 1, at winter 2 follow-up (and again at mid-/post-treatment for those crossed-over), and at winter 3 follow-up. Primary efficacy analyses will test superiority of CBT-SAD over LT on depression recurrence status (the primary outcome). Mediation analyses will use parallel process latent growth curve modeling.

**Discussion:**

Consistent with the National Institute of Mental Health’s priorities for demonstrating target engagement at the level of Research Domain Criteria-relevant biomarkers, this work aims to confirm the targets and mechanisms of LT and CBT-SAD to maximize the impact of future dissemination efforts.

**Trial registration:**

ClinicalTrials.gov identifier: NCT03691792. Registered on October 2, 2018.

## Administrative information

Note: the numbers in curly brackets in this protocol refer to SPIRIT checklist item numbers. The order of the items has been modified to group similar items (see http://www.equator-network.org/reporting-guidelines/spirit-2013-statement-defining-standard-protocol-items-for-clinical-trials/).

This confirmatory efficacy R01 trial focuses on two non-pharmacological treatments that each work for some SAD patients: light therapy (LT; i.e., daily exposure to bright artificial light during the symptomatic months), and SAD-tailored group cognitive-behavioral therapy (CBT-SAD) [11]. Substantial evidence supports LT as an efficacious acute SAD treatment [12]. In our previously completed R01-level efficacy trial enrolling 177 adults with SAD, CBT-SAD and LT were very similar in terms of symptom improvement and the proportions in remission at post-treatment (47.6% CBT-SAD, 47.2% LT) [13]. However, two winters later, CBT-SAD was associated with significantly fewer depression recurrences (27.3% CBT-SAD, 45.6% LT) and lower depression severity than LT [14]. These findings suggest that slightly more than one-quarter of those treated with CBT-SAD and slightly less than half of those treated with LT have a depression recurrence, highlighting the need for reliable strategies for precision medicine in clinical practice. In the current project, we apply the experimental therapeutics approach to determine how each treatment works and to identify the best candidates for each. Consistent with the NIMH’s focus on biological endpoints, we will ascertain whether theoretically derived candidate biomarkers of each treatment’s target and effect are prescriptive of better outcomes in that treatment vs. the other.

#### Light therapy effectively treats acute sad and correction of circadian phase is mechanistic of its antidepressant effects

Light therapy (LT) is the established, most researched, acute SAD treatment. Meta-analyses show that 53% of SAD patients fully remit (and 47% do not) over an LT trial [15]. Clinical practice guidelines recommend solo LT as a first-line acute SAD treatment and reinitiating daily LT each fall from first symptom until spontaneous springtime remission [16, 17]. However, only 41% of those treated acutely with LT continue using it over subsequent winters [18]. Several studies support circadian rhythm disturbances in SAD patients, with their circadian phase occurring either later (phase delayed) or, less commonly, earlier (phase advanced) compared to their euthymic circadian phase position following remission with LT [19–22] or to healthy individuals in winter [19, 22]. As restoring the correct phase of circadian rhythms is supported as LT’s mechanism of action [15, 23–25], circadian phase measures are established biomarkers of LT’s target and effect. We will use the best established method, dim light melatonin onset (DLMO), along with wrist actigraphy, an objective measure of sleep/wake patterns, to calculate Phase Angle Difference (PAD) = DLMO–mid-sleep [21].

#### Normalizing retinal subsensitivity might also be mechanistic of LT

Reduced retinal sensitivity to light in winter is associated with SAD [26]. The melanopsin pathway, from the retina to the brain, is an initial input pathway that could lead to downstream changes in circadian entrainment [20], duration of nocturnal melatonin release [27], and seasonal variation in monoamine concentration [28]. In a diathesis-stress model of SAD, low winter light conditions may combine with a genetic diathesis (photopigment genetic variation) to cause melanopsin-driven retinal subsensitivity, leading to an insufficient central nervous system (CNS) signal to either properly entrain the circadian clock, or for non-circadian, direct effects of light on the CNS [29]. A reduced post-illumination pupil response (PIPR) [26, 30], i.e., a smaller net difference in pupil response to red vs. blue light reflex trials, is an established biomarker of melanopsin-driven retinal subsensitivity. Melanopsin-containing retinal cells are uniquely sensitive to blue light, leading to a sustained pupillary constriction when stimulated. The PIPR is a sustained pupillary constriction after lights off and has been linked to melanopsin cell firing through intracellular recording in primates, even when inputs from rods and cones are pharmacologically blocked [30]. The PIPR provides an elegant way to isolate melanopsin contributions from those of rods and cones, making the PIPR a viable candiate biomarker of LT’s target and effect. In a comparison of individuals with SAD and controls with no history of depression tested in winter and summer, the SAD group had a lower PIPR in winter than in summer, whereas controls did not differ across the seasons [31]. In addition, the SAD group had a lower PIPR than controls in winter, but the groups did not differ in summer.

#### CBT-SAD effectively treats sad, lowers risk of recurrence, and engages a cognitive target

CBT-SAD uniquely engages a potentially SAD-specific cognitive vulnerability as a target: seasonal beliefs, i.e., rigid and maladaptive beliefs about the seasons and light availability [32]. Seasonal beliefs distinguish between individuals with SAD vs. non-seasonal unipolar depression [32, 33]. Seasonal beliefs change significantly more over the course of CBT-SAD than during LT, and greater change towards more flexible seasonal beliefs during treatment mediates both improvements in depression symptoms during active treatment [34] and lower depression scores one and two winters following treatment [35]. This provides evidence that engagement of the seasonal beliefs target mediates CBT-SAD’s acute antidepressant effects and its enduring benefits over LT.

#### Targets and biomarkers of CBT-SAD’s response

Consistent with the experimental therapeutics perspective, the proposed work intends to map seasonal beliefs onto biomarkers of CBT-SAD’s target and effect. Evidence supports that CBT for non-seasonal depression works via altering mechanisms of maladaptive thought patterns. Sustained pupil dilation to emotional words, which indexes prefrontal control mechanisms associated with emotion regulation [36, 37], is a potential biological mechanism of CBT response. Sustained frontal gamma-band EEG responses to emotional stimuli indicates sustained elaborative emotional processing and potentially sustained regulatory effort [38], is a biomarker of depression [38], and represents another candidate biomarker of CBT for depression’s target and effect. In SAD, we propose that maladaptive thoughts are dominated by seasonal- and light-related themes, matching the content of seasonal beliefs that appear mechanistic of CBT-SAD. Therefore, we will explore whether pupil dilation and EEG responses to seasonal words change more during CBT-SAD than LT (target engagement) and whether these changes are prescriptive of better outcomes in CBT-SAD than in LT, in the way that seasonal beliefs are. Such findings would indicate that patients who do not recur following CBT-SAD are less emotionally reactive to seasonal stimuli, thereby engaging in less elaborative processing of these stimuli and requiring less prefrontal control to regulate their emotional responses to them.

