### Objectives {7}

Our goal is to inform evidence-based guidelines for personalized medicine using CBT-SAD and LT, specifically for determining [1] which patients are best suited for which type(s) of treatment in terms of recurrence prevention, and [2] whether the selected treatment engages its intended target. We will ascertain whether theoretically derived candidate biomarkers of each treatment’s target and effect are prescriptive of better outcomes in that treatment vs. the other. We will examine the established chronobiological biomarker of LT’s target and effect, PAD, and explore the PIPR as a candidate biomarker of melanopsin-driven retinal subsensitivity with specificity to LT. We will use self-reported seasonal beliefs as the established target and mechanism of CBT-SAD and also map this construct onto theoretically relevant biomarkers of reduced emotional reactivity to seasonal stimuli, pupil dilation and sustained frontal gamma band EEG responses to seasonal words. In addition to determining whether these interventions engage associated change mechanisms, we will test the efficacy of a “switch” decision rule upon recurrence the next winter to inform clinical decision-making for managing SAD recurrences following a first-line treatment.

In this confirmatory efficacy R01, adults with SAD (target *N* = 160) will be randomized to two equal-probability 6-week treatment conditions in winter 1: CBT-SAD or LT. We will follow subjects in winter 2 and if a depression recurrence occurs, we will cross them over into the alternate treatment (i.e., switch to CBT-SAD upon recurrence after LT, switch to LT upon recurrence after CBT-SAD). All subjects will be assessed at follow-up in winter 3. Biomarker assessments will occur at pre-, mid-, and post-treatment in winter 1; at winter 2 follow-up (and again at mid- and post-treatment for those with depression recurrences crossed-over into the other treatment); and at winter 3 follow-up. This work will yield longitudinal data on targets, their engagement, and stability, thereby increasing the impact of future dissemination efforts.

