Specific aims are:To confirm the superiority of CBT-SAD over LT on depression recurrence status (the primary outcome)To elucidate differential mechanisms of acute treatment effects in CBT-SAD vs. LT by examining candidate biomarkers as potential mediators and to assess whether biomarkers at baseline, changes during treatment, and stability of changes over time are predictive of acute and/or long-term outcomes (recurrences)To compare a switch to CBT-SAD for those who recurred after LT to a switch to LT for those who recurred after CBT-SAD. We expect that a switch from LT➔CBT-SAD will show advantage over a switch from CBT-SAD➔LT in depression recurrences at winter 3, based on prior findings for greater durability in CBT-SADTo examine mediators of the effect of CBT-SAD on outcomes at winter 2 and winter 3

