### Sample size {14}

With a target *N* = 160 (80 subjects in each of the two treatments), the study will have 80% power to detect main effect differences of 22% (e.g., 28% vs. 50%) in winter 2 recurrence, which we expect at a naturalistic follow-up [14, 44]. Sample sizes for comparisons of winter 3 recurrence will depend on the number of recurrences at winter 2. Based on the recurrence rates observed in our prior study, we project that there will be about 37 recurrences in the LT group and 22 recurrences in the CBT-SAD group. This will provide 80% power to detect a difference in winter 3 recurrence of 35% (e.g., 60% vs. 25%) between CBT-SAD➔LT and LT➔CBT-SAD and a difference of 27% (e.g., 23% vs. 50%) between CBT-SAD and LT subjects without winter 2 recurrence. For biomarker comparisons, there will be 80% power to detect differences of 0.45 standard deviation (SD) in post-treatment values or in pre-post treatment changes between CBT-SAD and LT. Power for detecting relationships between biomarkers and outcomes were based on the odds ratio associated with an increase of 1 SD in the biomarker value or its change. For post-treatment remission, there will be 80% power to detect an OR of 2.2 in the CBT-SAD or LT group and a 2.4-fold difference in the ORs for the two treatments. For winter 2 recurrence, there will be 80% power to detect an OR of 2.2 in the LT group, an OR of 2.8 in the CBT-SAD group, and a 2.9-fold difference in their ORs. There was minimal attrition (4.5%) in our previous study, and we anticipate similar retention in this study. However, with attrition as high as 20%, there will be 80% power to detect a difference in winter 2 recurrence of 24% between CBT-SAD and LT and a difference of 39% in winter 3 recurrence between the two switch groups. Empirical sample size estimates^21^ indicate that the study will have at least 80% power to detect a mediated effect if the regression coefficient for the direct effect of treatment after adjustment for the mediator is at least .39 and the coefficients for the effect of treatment on the mediator and the effect of the mediator on outcome after adjustment for treatment are at least .26.

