To examine mechanistic differences between CBT-SAD and LT, mixed effects linear regression with subject as a random effect will be used to model biomarker changes during treatment as a function of time, treatment, and their interaction. We will also model the relationship between biomarker change and change depressive symptoms as a function of treatment by letting the regression coefficient differ between CBT-SAD and LT. This will provide a test of whether potential mediators of effect are treatment-specific. The predictive value of biomarkers at baseline, their pre-post treatment change, and the persistence of the change at follow-up will be examined using logistic regression (for post-treatment remission and winter 2 recurrence) and linear regression (for SIGH-SAD and BDI-II scores) with post-treatment and winter 2 outcomes as dependent variables. Interactions between the biomarkers and treatment will be used to test if the associations with outcomes differ in the CBT-SAD and LT groups. Adherence will be included in ancillary analyses to test its effect on the relationships of treatment with biomarkers and LT or CBT-SAD outcomes. The relationships between biomarkers and outcomes will be validated by examining how well they predict post-treatment and winter 3 outcomes for subjects who experience a recurrence at winter 2 and are switched to the alternative treatment. Data from the cross-over subjects will also be analyzed using mixed linear regression to compare within-person differences in pre-treatment biomarkers and their changes during their initial and subsequent treatments. Treatment, time point (winter 1 or 2), and their interaction will be included to test the effect of treatment sequence on within-person differences in biomarker responses to CBT-SAD and LT.

##### Aim 3

Logistic and linear regressions similar to those for Aim 1 will be used to compare the effect of switching from CBT-SAD➔LT versus LT➔CBT-SAD on winter 3 recurrence and depression scores. Post hoc adjustment for any differences between switch groups in baseline characteristics, treatment response, and biomarker profiles will be done by including them as covariates. Mixed linear regression will be used to longitudinally model depression scores over the three winters, with treatment as a time-varying covariate.

##### Aim 4

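### Biomarker change during treatment is called prescriptive, and the plan does not say that only the pre-treatment biomarker × treatment interaction can show who suits which treatment

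*Protocol article*

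**What the plan says.** Four parts of the protocol article bear on this.

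- **Purpose.** Background and rationale {6a} says the project is meant "to determine how each treatment works and to identify the best candidates for each", and asks whether candidate biomarkers are prescriptive of better outcomes in one treatment than in the other. Objectives {7} gives as goal [1] deciding "which patients are best suited for which type(s) of treatment in terms of recurrence prevention", and repeats the prescriptive question in the next sentence. Target engagement is a separate goal [2].
- **Change as a prescriptive marker.** The section on targets and biomarkers of CBT-SAD's response first asks whether pupil and EEG responses to seasonal words change more under CBT-SAD than under LT. It then asks "whether these changes are prescriptive of better outcomes in CBT-SAD than in LT", and likens this to the role of seasonal beliefs.
- **Analysis.** Under Aim 2 in Statistical methods {20a}, "The predictive value of biomarkers at baseline, their pre-post treatment change, and the persistence of the change at follow-up will be examined" by logistic and linear regression, with post-treatment and winter 2 outcomes as dependent variables. Then: "Interactions between the biomarkers and treatment will be used to test if the associations with outcomes differ in the CBT-SAD and LT groups". The three marker forms are not separated. The Aim 2 statement in Objectives {7} groups them in the same way: "assess whether biomarkers at baseline, changes during treatment, and stability of changes over time are predictive of acute and/or long-term outcomes".
- **Power.** Sample size {14} bases power on the "odds ratio associated with an increase of 1 SD in the biomarker value or its change", so one calculation serves both forms.

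**The concern.** A marker that guides the choice of treatment must be known before treatment is chosen. Pre-post change is not. It is produced in part by the treatment assigned, and change under CBT-SAD is a different quantity from change under LT. Participants with equal change in the two arms are therefore not comparable groups, although the arms as a whole are.

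Persistence is further removed. Biomarkers at follow-up are collected at the January winter 2 assessment, where recurrence is also determined, so persistence cannot inform the initial choice.

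What is at stake is the conclusion on goal [1]. If a change × treatment interaction is significant and the word prescriptive is carried into the report, a finding about how CBT-SAD works could be read as guidance on who should receive it.

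**Working it through.** **1. What each interaction estimates.** Let Y(1) and Y(0) be a participant's outcome under CBT-SAD and LT, D(1) and D(0) the biomarker change under each, and B the pre-treatment value.

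- Selection needs E[Y(1) − Y(0) | B = b]. The pre-treatment assessment ends with randomisation, so B precedes assignment. The contrast E[Y | CBT-SAD, B = b] − E[Y | LT, B = b] is then a randomised comparison at each b, and the baseline × treatment interaction shows whether it varies with b.
- The change × treatment model compares E[Y(1) | D(1) = d] with E[Y(0) | D(0) = d]. These condition on different variables in different sets of people. Unequal slopes show that change tracks outcome differently in the two arms. They do not show that anyone would do better in one arm.

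**2. Does the cross-over supply the missing quantity?** Only in part. Sample size {14} projects about 37 + 22 = 59 winter 2 recurrences, whose participants are offered the other treatment, and Aim 2 compares their biomarker changes under both. That subset is selected on recurrence, and its second treatment falls in a later winter. Validating the biomarker–outcome relations in it therefore does not turn change into a selection marker.

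**3. Reproducing the protocol's figure.** Inputs: 80 per arm and a 2.9-fold detectable ratio of odds ratios for winter 2 recurrence at 80% power (Sample size {14}); recurrence of 27.3% and 45.6% (prior trial, Background {6a}). Two-sided 5% is assumed, since the article states no alpha.

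Closed form: ratio = exp[(1.960 + 0.842) × √(Σ 1/(n p q))].

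- Winter 2, n = 80: 1/(80 × 0.273 × 0.727) + 1/(80 × 0.456 × 0.544) = 0.0630 + 0.0504 = 0.1134; exp(2.802 × 0.3367) = 2.57.
- Winter 2, n = 64 (20% attrition): 2.87.
- Post-treatment remission, 47.6% and 47.2%, n = 80: 2.43, against a stated 2.4.

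The closed form takes the variance as if the slopes were zero. Simulation avoids that: 4,000 trials per setting, a logistic model with treatment, marker and product, a Wald test on the product, and odds ratios per SD of 2.9 in CBT-SAD and 1.0 in LT. Power was 0.79 with no arm difference in mean change and 0.81 with a difference of 0.45 SD. The stated 2.9 is reproduced.

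**4. Both interactions in the same simulated trials.** Recurrence depends on change in the CBT-SAD arm only. The baseline marker is set unrelated to change, outcome and treatment effect.

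| Odds ratio per SD of change, CBT-SAD (LT = 1.0) | Change × treatment significant | Baseline × treatment significant |
|---|---|---|
| 2.9 | 79–81% | 5.0–5.4% |
| 2.8 | 78% | 4.8–5.0% |
| 2.2 | 56–58% | 4.8–4.9% |
| 1.5 | 20–22% | 4.6–5.7% |

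Ranges span the two settings for the mean shift. The middle column is how often a change interaction would be detected when the baseline marker is assumed to have no selection value. The last column is the nominal error rate, as it should be.

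**The case against.** The strongest reply is that this is one loose word in a background section. That section is framed as exploration. Its model, seasonal beliefs, is described in the preceding text as a mediator. The conclusion it draws from a positive result is mechanistic: patients who do not recur after CBT-SAD react less to seasonal stimuli. The Aim 2 analysis uses neither prescriptive nor best candidates, opens by speaking of mechanistic differences, and says the interactions test whether associations differ by arm, which they do. The one clinical use stated for the pupil and EEG measures, in the section on self-report measures, is checking engagement. The baseline interaction is planned and powered.

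Most of this stands, and it rules out three stronger readings that a reader might infer:

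- *That the selection objective has no valid test.* It has one: the baseline × treatment interaction.
- *That the trial has a rule naming candidates from change scores.* No section states one. The risk comes from reading the background, objectives and Aim 2 together.
- *That 79–81% is a rate of false selection claims.* It is power for a true arm-specific association that was built into the simulation. The absence of any baseline association is also an assumption; nothing in the article supports or refutes it.

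What the reply does not remove is that the article uses one term both for changes during treatment and for patient suitability, and nowhere says that suitability rests on pre-treatment values alone. The comparison with seasonal beliefs adds to the ambiguity, because the evidence cited for them is greater change and mediation, not a baseline interaction.

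**Conclusion.** The point holds in a limited form. Changes during treatment are described as prescriptive, the same term is tied to best candidates and patient suitability, and the Aim 2 analysis does not say which of its three interactions can answer goal [1]. Only the pre-treatment one can. Using change for target engagement and mediation under Aims 2 and 4 is legitimate, and the primary comparison, randomisation and sample size are untouched.

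The argument about change and persistence follows from when they are measured and needs no numerical assumption. The simulation only illustrates how far the two tests can diverge: 79–81% against about 5% at the protocol's design effect, narrowing to 20–22% against about 5% at an odds ratio of 1.5 per SD. It assumes a normally distributed marker, two-sided 5%, an association confined to the CBT-SAD arm, a baseline marker with no selection value, and 80 analysed per arm.

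This merits correction because it governs what the trial may conclude on a stated objective.

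**What to change.** - **Targets and biomarkers of CBT-SAD's response:** describe the planned test of changes in mechanism or mediation terms instead of calling changes prescriptive.
- **Background and rationale {6a}, Objectives {7} and the Aim 2 analysis:** add a statement to this effect: *Conclusions on which patients suit which treatment will rest only on interactions between treatment and biomarkers measured before treatment. Interactions involving pre-post change or persistence will be reported as mechanism or within-arm association, with no treatment-selection conclusion.*
- **Switched participants:** apply the same limit when their data are used for validation.

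No model, visit, measurement or sample size changes. The cost is that fewer tests can support the personalised-medicine claim.
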